##### Emotion regulation questionnaire

The ERQ was developed by Gross and contains a total of 10 items in 2 dimensions, a CR and expression inhibition (EI) (Gross and John, 2003). It is scored through a 5-point scale (1 = strongly disagree and 5 = strongly agree); the higher the score, the more likely the subject is to use this emotion regulation strategy. The Chinese-translated version of the ERQ has good test–retest reliability (r = 0.82 and 0.79) and internal reliability (Cronbach’s alpha coefficient = 0.85 and 0.77) for the CR and EI subscales, split-half reliability (reliability = 0.87), and construct validity for the two-factor model (CFI = 0.96, RMSEA = 0.09), with completely standardized factor loadings of all items higher than 0. 55 at a statistically significant level (Wang et al., 2007). The ERQ will be utilized to verify the construct validity of the RIT indexes.

### Brain structure and functional imaging

Brain structure and functional imaging data will be collected on a Siemens 3.0T scanner from the affiliated hospital of the university. During the scan, each participant will be in a supine position, with foam under the head to minimize head movement, and will be wearing headphones to reduce noise interference. A standard orthogonal single-channel head coil will be used. Conventional T1WI and T2WI imaging, echo-planar imaging (EPI), and whole-brain 3D magnetization-prepared rapid gradient-echo (MPRAGE) imaging will be conducted for each subject by a radiologist. The experimental stimulus will be presented by connecting a liquid-crystal display (LCD) screen outside the scanning channel to the E-prime stimulus presentation and the response recording system, and each participant will view the presentation through a reflective mirror attached to the head coil. During the experiment, the participant will use a joystick to enter their ratings while the system automatically records the participant’s response to the CR tasks.

The scanning sequence will be as follows: **(1)** The axial T1-FLAIR sequence, parallel to the anterior-posterior joint line; pulse repetition time/echo time (TR/TE) = 500 ms/14 ms; slice thickness = 4 mm; field of view (FOV) = 240 mm × 240 mm; and matrix = 256 × 160; **(2)** sagittal T2-FLAIR will be scanned at the same location using gradient-echo echo-planar imaging (EPI) with the following parameters: TR/TE = 3,000 ms/40 ms; FOV = 240 mm × 240 mm; matrix = 128 × 128; 30 consecutive images at each time point; and slice thickness = 4 mm; if no abnormality is observed in plain scans, resting-state scans will be performed; **(3)** a total of 176 consecutive slices in the sagittal position will be acquired to cover the entire brain through an MPRAGE sequence for subsequent 3D reconstruction and spatial alignment with the following parameters: TR/TE = 1,970 ms/3.93 ms; flip angle = 15°; slice thickness = 1.70 mm; interval = 0.85 mm; FOV = 250 mm × 250 mm; and matrix = 448 × 512; and **(4)** task-state blood-oxygen-level-dependent (BOLD) functional images will be acquired using the EPI sequence, with the same position as that for anatomical images and the following parameters: TR/TE = 2,000 ms/30 ms; number of slices = 36; slice spacing = 33; FOV = 240 mm × 240 mm; and matrix = 64 × 64.

Regions of interest (ROIs): The structural and functional activities of the dlPFC, the vlPFC, the dmPFC, and the vmPFC, as well as the amygdala, will be analyzed. The functional connectivities between these regions and subcortical regions (amygdala) will be analyzed based on the time series of these ROIs.

### Statistical analysis

#### Behavioral and self-report data

##### Intervention effect analysis

A 3 (group: CR = cognitively vulnerable intervention subgroup; WC = cognitively vulnerable waiting-list control subgroup; NC = normal control group) × 3 (time point: T_0_ = pretraining, T_1_ = post-training, T_2_ = 6-month follow-up) mixed design will be adopted. Using the HLM analysis, as well as mediating/modulating effect analyses, we will investigate (1) hypothesis 1, whether the changes in negative cognitive biases and depressive symptoms across time 1 and time 2 differ significantly among groups and (2) hypothesis 2, whether the changes in negative cognitive bias (negative interpretation bias and/or negative rumination bias) pre- and post-training could predict depression symptoms at T_1_ and/or T_2_.

To test hypothesis 1, we will conduct an HLM analysis with time (0 = pretraining; 1 = post-training), group (0 = CR; 1 = WC; 2 = NC), and the interaction between time and group as predictor variables and the with CESD score as the outcome variable. To test hypothesis 2, we will conduct mediating/modulating effect analyses among CR ability (RIT) and tendency (ERQ), negative cognitive bias (NCPBQ), cognitive vulnerability (CSQ), and depressive symptoms (CESD) at T_1_ and/or T_2_. The HLM and mediating/modulating effect analyses will be conducted in SPSS (Statistical Product and Service Solutions) software version 22.0 (SPSS, Inc., Chicago, IL, United States) combined with the PROCESS Macro (Hayes, 2012).

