#### Neural mechanism of improvements in cognitive reappraisal inventiveness in individuals cognitively vulnerable to depression through cognitive reappraisal training

Using the group of individuals cognitively vulnerable to depression (divided into intervention and waiting subgroups) and the normal control group as research participants, we will conduct a 4-week (2 sessions/week) CR training program for the intervention subgroup, and before and after training, the intervention and waiting-list control subgroups will undergo fMRI to examine whether CR training can improve reappraisal inventiveness and depression symptoms by regulating the function of the prefrontal–amygdala circuit.

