#### Short- and long-term antidepressant effects of cognitive reappraisal training on individuals cognitively vulnerable to depression

Through follow-up immediately after intervention or 6 months after the intervention, we will validate the hypothesis of the reduction in cognitive vulnerability to depression and depression symptoms through improvements in reappraisal inventiveness with CR training by constructing a hierarchical linear model (HLM) analysis and mediating/modulating effect analyses.

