(3) Functional connectivity analysis: Taking the amygdala as the seed point and the average time series within the seed point as the reference time series, we will perform “one point to multipoint” linear correlation analysis with the time series of each ROI. Using the average signals of head movement, the white matter, the cerebrospinal fluid, and the whole brain as covariates and using the prefrontal-amygdala FCs as predictors of depressive symptom scores, we will use between-group *t*-tests, combined with correlation analyses and path analyses, to examine (1) whether the FCs between the prefrontal subregions (dlPFC/vlPFC/dmPFC/vmPFC) and the amygdala before and after CR training differ significantly and (2) if the prefrontal-amygdala FCs do differ significantly, whether the FCs could predict depressive symptoms (T_1_ and T_2_). The FCs between ROIs, cognitive bias (CSQ/NCPBQ), CR ability (RIT), and tendency (ERQ) will then be entered into path analyses to verify the cognitive bias model of CR training.

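### Hypothesis 1 covers cognitive bias as well as depressive symptoms, but the one model written to test it has CESD as its only outcome and no mediation or path analysis lists arm

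*Protocol article*

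**What the plan says.** Under Intervention effect analysis, hypothesis 1 is stated on two outcome domains: "whether the changes in negative cognitive biases and depressive symptoms across time 1 and time 2 differ significantly among groups". Hypothesis 2 turns to prediction, asking whether change in bias over training "could predict depression symptoms at T_1_ and/or T_2".

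The next paragraph gives one model for hypothesis 1. Its predictors are coded as "time (0 = pretraining; 1 = post-training), group (0 = CR; 1 = WC; 2 = NC", and it ends with "the interaction between time and group as predictor variables and the with CESD score as the outcome variable". For hypothesis 2 it announces mediation and moderation analyses among RIT, ERQ, "negative cognitive bias (NCPBQ), cognitive vulnerability (CSQ), and depressive symptoms (CESD) at T_1_ and/or T_2".

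Three other places bear on the point.
- The procedure section on short- and long-term effects plans to "validate the hypothesis of the reduction in cognitive vulnerability to depression and depression symptoms". The same sentence goes on to name HLM together with mediation and moderation analyses as the method.
- The procedure section on the neural mechanism describes the pre- and post-training comparison as designed "to examine whether CR training can improve reappraisal inventiveness and depression symptoms".
- The functional connectivity part of Data analysis says that, along with the connectivities, "cognitive bias (CSQ/NCPBQ), CR ability (RIT), and tendency (ERQ) will then be entered into path analyses".

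The last paragraph of the Introduction groups NCPBQ-NIB, NCPBQ-NRB and CSQ as the negative cognitive biases. Secondary outcomes places CSQ and NCPBQ under that same label.

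**The concern.** The hypothesis and the model written to test it have different outcomes. This is more than a detail left for an analysis plan, because the article itself names the model and fixes its outcome. An analysis plan that copied the sentence would carry the contradiction forward.

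The trial's cognitive bias model says that training lowers bias and that lower bias relieves symptoms. The effect of training on bias is the link that randomisation can support directly. An association between bias and CESD cannot show that training moved bias. If the text is followed literally, a CESD effect could be read as support for the whole chain although no comparison of the randomised arms on bias was specified. Choosing the bias model later also leaves room to pick among measures, and the text already allows interpretation bias and/or rumination bias.

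**Working it through.** No figure in the plan depends on this point, so there is nothing to reproduce. The check sets each measure against the analyses that could give a comparison of the intervention (CR) and waiting-list (WC) arms.

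**Step 1: outcomes that hypothesis 1 covers.** Depressive symptoms means CESD. Negative cognitive biases means NIB, NRB and CSQ by the Introduction's grouping. NIB and NRB are clear. CSQ is slightly less so, because the hypothesis 2 sentence lists it as cognitive vulnerability, apart from NCPBQ. RIT is not named in hypothesis 1.

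**Step 2: where group or arm enters a stated analysis.**

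| Analysis | Group or arm stated? | Outcome or variables |
|---|---|---|
| HLM for hypothesis 1 | yes, CR, WC and NC | CESD only |
| Mediation and moderation for hypothesis 2 | not listed | RIT, ERQ, NCPBQ, CSQ, CESD |
| Path analyses | not listed | connectivities, CSQ/NCPBQ, RIT, ERQ |
| Between-group *t*-tests | yes | connectivities |
| Group comparison of ROI volumes | yes | volumes |
| RIT comparison before training | vulnerable against normal control | RIT, not a randomised contrast |

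The NCPBQ paragraph under Secondary outcomes assigns NIB and NRB only to the mediation analyses.

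**Step 3: count.** Specified group-by-time models: CESD 1; NIB 0; NRB 0; CSQ 0. So 1 of the 4 measures under hypothesis 1 has one, or 1 of 3 if CSQ is left out. RIT, which the neural mechanism section wants to see improved, also has 0.

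**Step 4: does any general statement fill the gap?** The lead-in to the hypotheses attaches HLM and mediation jointly to both hypotheses, and the short- and long-term section attaches HLM to cognitive vulnerability. Both show intent. Neither names a bias outcome with a group term, and the sentence that does specify a model names CESD alone.

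**The case against.** The strongest reply is that the intent is plain and the article is condensed. HLM is tied to bias and cognitive vulnerability in two places. The CESD sentence can be read as spelling out only the primary outcome, with secondary models left to a fuller document. Aim 2 makes training the start of the mediation chain, and a mediation with training as exposure estimates a training-to-bias path. Limitations also says that the bias process measures are to be interpreted as exploratory.

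Much of this stands. It rules out some stronger readings that a reader might infer:
- That the trial will have no randomised estimate for bias, or that a null effect on bias would go unseen. The documents do not support this, because aim 2 implies an estimate through the mediation. What holds is that the estimate is not specified: the variable lists omit arm.
- That RIT is an untested part of hypothesis 1. It is not in that hypothesis, although the neural mechanism section asks whether training improves it.
- That the sample size section gives these outcomes about 66% power. The d of 0.39 comes from depression scores, the 66% assumes a two-sided 0.05 level that the article does not state, and it is before any multiplicity correction. The matching standard error, sqrt(2/75) = 0.163 SD, is for a single time point. For a difference in change, in baseline-SD units with equal variances, it is 0.163 × sqrt(2(1 − ρ)), which equals 0.163 only if the pre-post correlation ρ is 0.5. No ρ is given.

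The reply does not reconcile the text. One model follows the words that introduce the test of hypothesis 1, and its outcome is narrower than the hypothesis.

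**Conclusion.** The point holds as an internal contradiction of limited weight. As written, the bias part of hypothesis 1 (NIB, NRB and, on the Introduction's grouping, CSQ) has no specified between-arm estimate, while CESD has one. The conclusion rests on reading the model sentence and the variable lists as they stand. It would lapse if a fuller protocol or analysis plan names these outcomes and puts arm into the mediation. The exploratory status given in Limitations lowers the weight but does not remove the mismatch, because a measure named in a hypothesis still needs a stated contrast. No power or precision figure for the bias outcomes can be drawn from the documents.

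**What to change.** In Intervention effect analysis:
1. State that the same time-by-group model is fitted to CESD as primary outcome and, as secondary outcomes of hypothesis 1, to NCPBQ-NIB, NCPBQ-NRB and CSQ.
2. For each, report the CR-minus-WC difference in change with its interval. Name that contrast, because the group factor also contains the non-randomised normal controls.
3. State arm (CR against WC) as the exposure in the mediation analyses.
4. Label the bias results exploratory, in line with Limitations, or state a multiplicity rule. No particular correction is required.
5. Optionally report the same model for RIT, as an answer to the question in the neural mechanism section and not as part of hypothesis 1.

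The cost is wording and three further model fits, or a few more with RIT, on measures already planned. The downside is more secondary tests to interpret. The Ethics statement says that nobody had been recruited at submission, so on the article's own account the wording could be settled before any data existed.

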#### Group of individuals cognitively vulnerable to depression

Of the recruited healthy subjects, those with an average weakest link score plus 1 standard deviation will be assigned to the group of individuals cognitively vulnerable to depression, and whether they have affective disorders and other axis I diseases will be determined by two experienced psychiatrists using the Structured Clinical Interview for DSM Disorders (SCID).

The inclusion criteria are as follows: participants (a) with average CSQ weakest link score plus 1 standard deviation; (b) with Han ethnicity; (c) aged 18–25 years; (d) who are right-handed; (e) with normal or corrected vision; (f) who are local community residents; (g) who can understand the content of the study, are willing to participate, and are committed to completing the entire experiment; (h) have signed informed consent form.

The weakest link composite score of CSQ will be calculated as follows: (1) calculating the scores for the 3 subscales (causes, consequences, and self-worth) of CSQ; (2) standardizing the scores for the 3 subscales and converting them to standard scores, based on which the standard scores for the 3 subscales for each individual are then ranked, in which the highest of the 3 subscale scores represents the final score for each individual’s weakest link; and (3) calculating the average weakest link scores for all individuals. The score is further used to screen individuals in the cognitively vulnerable to depression group (mean score plus 1 standard derivation) or those in the not cognitively vulnerable to depression group (the mean score minus 1 standard derivation).

The exclusion criteria are as follows: participants (a) who meet the diagnostic criteria for depression or other axis diseases; (b) with a history of taking any antidepressants or antipsychotics; (c) with a history of alcohol or drug abuse or dependence; (d) with a history of central nervous system diseases, e.g., head injury or epilepsy; (f) with a history of multiple sclerosis or major physical diseases; (g) with a history of electroshock therapy; (h) with a history of mental illness in first-degree relatives; and (i) with contraindications to MRI.

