#### Normal control group

Of the recruited healthy subjects, those with an average weakest link score minus 1 standard deviation will compose the group of individuals without cognitive vulnerability to depression, i.e., the normal control group. Individuals in the normal control group will be interviewed by two experienced psychiatrists using the SCID to exclude those suffering from depression and other axis I diseases. Ultimately, the control group will comprise 30 subjects, and the control group and the intervention and waiting subgroups of the group of individuals cognitively vulnerable to depression will be homogenous in terms of demographic variables and depression symptoms.

The inclusion criteria are described as follows: participants (a) with average CSQ weakest link score minus 1 standard deviation; (b) with Han ethnicity; (c) aged 18–25 years; (d) who are right-handed; (e) who have normal or corrected vision; (f) who are local community residents; (g) who can understand the content of the study, are willing to participate, and are committed to completing the entire experiment; and (h) who signed an informed consent form.

The exclusion criteria are described as follows: participants (a) who meet the diagnostic criteria for depression or other axis diseases; (b) history of taking any antidepressants or antipsychotics; (c) history of alcohol or drug abuse or dependence; (d) history of central nervous system diseases, e.g., head injury or epilepsy; (e) history of multiple sclerosis or major physical diseases; (f) history of electroshock therapy; (g) history of mental illness in first-degree relatives; and (h) contraindications to MRI.

Sample size calculation: An *a priori* power analysis found that a sample size of 75 participants per group (*N* = 150) would be sufficient with a medium effect size (Cohen’s d = 0.0.39) and 65% power (computed with G*power 3.1). These estimates were based on previous research examining changes in HRSD/BDI-II scores before and after CR training when compared to the waiting-list control condition (Berking et al., 2019). Since the sample size projection considered an anticipated 20% dropout rate, the target sample size was 188 patients.

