Randomization to treatment will be completed with a computer-generated list of random numbers, and each participant will be randomly assigned to either the intervention group or the control group with a 1:1 allocation and double-blinded. The randomization will minimize group differences in demographic factors and instrument scores (Pocock and Simon, 1975).

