### Secondary outcomes

#### Negative cognitive bias

##### Cognitive style questionnaire

The CSQ will be used to screen subjects in the group of individuals cognitively vulnerable to depression and the group of individuals not cognitively vulnerable to depression. The CSQ was developed based on the hopelessness theory and was designed to be used to assess an individual’s negative cognitive styles, mainly including the individual’s perceptions of the causes, consequences, and self-worth after an event. The Chinese-translated version of the CSQ has good internal reliability (Cronbach’s alpha coefficient = 0.94), satisfactory 8-week test–retest reliability (reliability = 0.59), and good construct validity for the four-factor model (CFI = 0.91, RMSEA = 0.09), which included general-local causes, stable-temporary causes, consequences, and self-worth (Chen et al., 2014).

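### Hypothesis 1 is tested by a three-group × time interaction that includes non-randomised normal controls, so it can be significant without a training effect and is not the comparison the sample size was based on

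*Protocol article*

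**What the plan says.** All of this is in the protocol article.

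- **Test.** *Intervention effect analysis* sets out a three-group by three-time mixed design. Hypothesis 1 asks "whether the changes in negative cognitive biases and depressive symptoms across time 1 and time 2 differ significantly among groups". The hierarchical linear model has time (pre, post), "group (0 = CR; 1 = WC; 2 = NC), and the interaction between time and group as predictor variables", and CESD as outcome. That section names no CR-versus-WC contrast as the test of training.
- **Who is randomised.** The *Procedure* section divides only the vulnerable group into intervention and waiting subgroups. Participants are "randomly assigned to either the intervention group or the control group with a 1:1 allocation".
- **How the groups are formed.** For the vulnerable group, "those with an average weakest link score plus 1 standard deviation will be assigned to the group of individuals cognitively vulnerable to depression". For NC, "those with an average weakest link score minus 1 standard deviation will compose the group of individuals without cognitive vulnerability to depression". Further, "the control group will comprise 30 subjects", and NC, CR and WC "will be homogenous in terms of demographic variables and depression symptoms".
- **Sample size.** 75 per group (N = 150), 65% power, an effect size printed as 0.0.39 (read here as 0.39), and 188 after 20% dropout. It is based on change under CR training compared with a waiting list.
- **CSQ stability.** The CSQ is reported to have "satisfactory 8-week test–retest reliability (reliability = 0.59").

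**The concern.** An interaction across three groups has a null hypothesis with two parts: CR and WC change alike, and NC change like them. Randomisation supports only the first part. Rejection can come wholly from the second, and NC were built in a way that makes different change plausible. They are taken from the other end of the CSQ, then made similar to the vulnerable arms on observed depression symptoms. If the CSQ and CESD are correlated, the two populations have different CESD means. NC who match the vulnerable arms at baseline would then be untypically high for their population, or the vulnerable participants untypically low for theirs, and the groups would drift apart on remeasurement.

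CESD is the primary outcome, so a significant result on the test as written could not by itself be attributed to training. The written test also answers a different question from the one the sample size addresses.

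**Working it through.** **1. The plan's own figure.** Inputs: n = 75 per group, d = 0.39; two-sided alpha of 0.05 is assumed because none is stated. Noncentrality = 0.39 × √(75/2) = 2.39; critical t on 148 df = 1.976; power = 66.0% (normal approximation 66.6%), against 65% stated. Dropout: 150/(1 − 0.20) = 187.5, so 188. Both reproduce as a two-group calculation.

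**2. Three-group test with no training effect.** With two time points and complete data, the group × time test is a one-way F test on change scores. Let CR and WC have equal mean change and let NC differ by δ, in SD of change. With n = 75/75/30 the noncentrality is λ = (150 × 30/180) × δ² = 25δ², on 2 and 177 df, critical F = 3.05.

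| δ | 0 | 0.2 | 0.3 | 0.4 | 0.5 | 0.6 | 0.8 |
|---|---|---|---|---|---|---|---|
| Rejection | 5% | 13% | 25% | 41% | 60% | 76% | 95% |

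**3. What δ could be for CESD.** The article gives neither the CSQ–CESD correlation ρ nor the CESD retest correlation r; both are assumed here. The mean of a standard normal variable beyond +1 SD is φ(1)/(1 − Φ(1)) = 1.525. If the groups are matched on observed CESD and then move back towards their own population means, the gap in change is 2 × (1 − r) × ρ × 1.525. The SD of change is √(2(1 − r)), so δ = 1.525 × ρ × √(2(1 − r)).

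| ρ | δ at r = 0.7 | Rejection | δ at r = 0.5 | Rejection |
|---|---|---|---|---|
| 0.1 | 0.12 | 8% | 0.15 | 10% |
| 0.2 | 0.24 | 17% | 0.31 | 25% |
| 0.3 | 0.35 | 33% | 0.46 | 52% |
| 0.4 | 0.47 | 54% | 0.61 | 78% |
| 0.5 | 0.59 | 75% | 0.76 | 93% |

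A simulation that cut the groups at ±1 SD of CSQ and matched each NC individually on baseline CESD gave 17–27% at ρ = 0.2 and 37–99.6% at ρ = 0.3–0.5. Without matching, and with the correlations stable over time, it gave about 5%. The CR-versus-WC test on the same simulated data rejected in 4.8–5.8% of trials in every scenario.

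**4. CSQ, if it is tested in the same way.** With the article's retest value of 0.59 and the screening score used as the pretraining value, expected drift is 1.525 × (1 − 0.59) = 0.63 SD, downwards in CR and WC and upwards in NC. Rejection is then close to 100% with no training effect. If the CSQ is measured afresh at pretraining (classical error model, same reliability), the simulated drift from pre- to post-training is 0.00 SD.

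**5. Power if NC behave exactly like WC.** For a true CR–WC difference of 0.39, λ = 6.65 and the 2-df test has 62% power, against 66% for the two-group contrast.

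**The case against.** The strongest reply is that the randomised comparison can be identified elsewhere: the sample size is based on training against waiting list, allocation is 1:1 between two arms, and the imaging part of the procedure sets the two vulnerable subgroups side by side. With group as a factor and CR as reference, one interaction coefficient is exactly CR versus WC, and follow-up contrasts are often left to an analysis plan that is not shown. This limits the point to the wording of the test. It does not remove it, because the article itself states the criterion as a difference among three groups and does not say that claims about training rest on that coefficient.

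Three stronger readings are tempting, and the document does not support them.

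- **That a false positive is near certain.** That figure belongs to the CSQ and needs the screening score to serve as baseline, which is not stated. The written model uses CESD. The limitations section calls the cognitive-bias measures exploratory, and 0.59 is an 8-week value whereas training lasts 4 weeks.
- **That inflation for CESD is known to be large.** It rests on assumed correlations and on matching. The article promises homogeneous groups but describes no matching procedure, and both populations are screened to exclude depression.
- **That the 0/1/2 codes force the groups onto a straight line.** They would if entered as numbers: a true difference of 0.39 with no change in NC would then be estimated as 0.23. But the article describes group as a three-level factor, so the codes are most naturally read as labels.

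**Conclusion.** The point holds as a defect in the stated test. The hypothesis 1 criterion mixes one randomised contrast with non-randomised ones, can be met when CR and WC do not differ, and departs from the comparison the sample size rests on.

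The size for CESD is open: 5% false rejection if NC change like the vulnerable arms, and anywhere from about 8% to 93% over assumed CSQ–CESD correlations of 0.1–0.5, with CESD retest of 0.5–0.7, matching on observed CESD, 75/75/30 participants and two-sided 0.05. A near-certain false rejection applies only if the CSQ is tested this way with the screening score as baseline. The wording should be corrected before analysis, but the document does not establish that the primary test will be badly inflated.

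**What to change.** In *Intervention effect analysis*:

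1. State that group is a categorical factor.
2. Name the 1-df CR-versus-WC × time contrast, among randomised participants, as the confirmatory test of hypothesis 1.
3. Use NC for the pretraining RIT comparison and as a descriptive benchmark, and state that differences in change between NC and either vulnerable arm are not evidence of a training effect.
4. If the CSQ is analysed for change, say whether the pretraining value is the screening score or a new measurement.

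This restores a false-positive rate of about 5% and the planned power of about 66% at d = 0.39. It changes wording only; recruitment and data collection stay as they are. The price is that claims from CR-versus-NC change are given up.
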